### Characteristics of participants

The inclusion criteria include the following: T2DM of more than one year of disease duration, age between 30 and 80 years, HbA1c > 9% in the last test performed in the 12 months prior to study inclusion, with no change in antidiabetic treatment within the previous 3 months. The changes in the dose of a drug in the antidiabetic treatment will be not considered as exclusion criteria.

The exclusion criteria include the following: T2DM controlled by endocrinologist at the moment of inclusion, systemic glucocorticoid treatment (ATC code: H02AB) or orlistat treatment (ATC code: A08AB01) (chronic or during the two months prior to inclusion), estimated life expectancy < 2 years, active treatment for malignancy (other than basal cell cancer or squamous cell skin cancer), serious mental disorders (psychosis, bipolar affective disorder, severe depressive episode with psychotic symptoms), class III or IV (New York Heart Association functional classification) heart failure (ICD-10: I50), dementia, renal transplantation or current dialysis treatment, history of drug and/or alcohol abuse (ICD-10: F10-F14), pregnancy or lactation, treatment with immunosuppressive drugs, haemoglobinopathies (ICD-10: D58.2), or chronic anaemia, body mass index (BMI) > 45 kg/m^2^, or any conditions that the investigator considered could prevent the patient from completing the study.

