##### Study variables

The variables are collected at different time-points during the study (Table 1). These include: sociodemographic variables (age, sex), anthropometric variables (height, weight, BMI, blood pressure), clinical variables (drugs and dosages), smoking habits (smoking, non-smoker, ex-smoker), presence of multiple disorders (Clinical Risk Group and identified in the computerized patient clinical history and the number of health problems as a proxy asset of multi-morbidity), presence of microvascular complications (diabetic retinopathy, diabetic nephropathy, and diabetic neuropathy), presence of macrovascular complications (ischaemic heart disease, stroke, peripheral vascular disease, and heart failure), laboratory variables according to the standard procedures of the laboratory of reference (HbA1c, blood count, renal function- creatinine, glomerular filtration rate, urinary excretion of albumin), liver function (Alanine Aminotrasferase (ALT), Aspartate Aminotransferase (AST), alkaline phosphatase, Gammaglutamil transferase (GGT)), lipid profile (total cholesterol, HDL-C, triglycerides, LDL-C, and non-HDL-C), and episodes of severe hypoglycaemia (episodes of hypoglycaemia that require the intervention of a third party for recovery will be recorded).

**Table 1 Tab1:** Study timeline, variables and procedures

	IG-1 and IG-2					Control group	
Data collected	Assessment (months)				Source	Assessment	Source
	0	3	6	12		Month 0 & Month 12	
Inclusion/Exclusion criteria	1 + 2	1 + 2	1	1 + 2	e-CRF	§	SIDIAP
Sociodemographic variables and comorbidities: *1. Age, height, gender, weight, BMI, duration of T2DM, medication (active component and dose),* etc.*...* *2. Pluripathology, clinical risk group*	1 + 2	1	1	1 + 2	eCAP	§	SIDIAP
Main variable: HbA1c	1 + 2	1	1	1 + 2	e-CRF eCAP	§	SIDIAP
Lipid profile and other laboratory variables: Total cholesterol, HDL, LDL, triglycerides, non-HDL, urea, creatinine, glomerular filtration rate, urine albumin, AST, ALT, FA, GGT. Systolic and diastolic blood pressure	1 + 2	1	1	1 + 2	eCAP e-CRF	§	SIDIAP
Smoking habit	1 + 2	1	1	1 + 2	eCAP e-CRF	§	SIDIAP
Sedentary lifestyle	1 + 2	1 + 2	1	1 + 2	e-CRF		
Detection of macrovascular complications *Ischaemic heart disease, stroke, peripheral artery disease, heart failure*	1 + 2	1	1	1 + 2	eCAP e-CRF	§	SIDIAP

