Chronic microvascular complications detection *Diabetic retinopathy, diabetic nephropathy (albuminuria, renal failure), diabetic neuropathy*.	1 + 2	1	1	1 + 2	eCAP e-CRF	§	SIDIAP
Costs: *Cost of medication, laboratory tests, additional tests, cost of staff (visits), referrals, IT*	1 + 2			1 + 2	eCAP e-CRF	§	SIDIAP
*Costs:* *Urgent care, outpatient and hospital admissions*	1 + 2			1 + 2	e-CRF		
Satisfaction and quality of life of patients *DTSQ / ESDQoL*	1 + 2		1	1 + 2	e-CRF		
Professional Satisfaction *Specific Questionnaire*				1 + 2	e-CRF		
intensification/treatment adherence		1 + 2	1	1 + 2	e-CRF		
Occurrence of severe hypoglycaemia episodes	1 + 2	1	1	1 + 2	e-CRF		SIDIAP
“Patient Activation Measure” questionnaire (instrument for disease self-evaluation)	1 + 2	1 + 2		1 + 2	e-CRF		

*For the IG-1 (monographic + training of professionals + additional measures originated in phase 1), clinic visits will be carried out at baseline, 3, 6, and 12 months. For the IG-2 (training of professionals + additional measures originated in phase 1), clinic visits will be carried out at the time of inclusion (month 0), 3, and 12 months*

Variables related to healthcare costs are also collected and include the costs derived from the medication used (cost per patient per month of medication prescribed according to prices set by the Health Ministry), laboratory tests used (based on prices listed in the Catalan Health Institute service portfolio), supplementary tests, professional costs (the cost of patient visits), cost derived from the referrals to specialists, use of the emergency department, outpatient and hospital admissions, temporary disability, and consumption of testing strips for measuring blood glucose.

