### Evaluation of the effectiveness in the three study groups

Data at baseline and at 12 months of the population of all three types of learning centres that meet the defined criteria for inclusion and exclusion will be compared. Criteria will be adequately defined using the ICD-10 codes, thoroughly specifying the temporary windows of the accepted values. Only the outcomes that include SIDIAP variables (as indicated in the Table 1) will be able to be evaluated; even those that are in the e-CRD will not be able to be assessed. This evaluation of effectiveness will be performed in two possible ways: i) following the patients who meet the inclusion criteria in 2015 until the end of the study in 2018 (cohort study), or ii) a cross-sectional study in 2015 and another in 2018.

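### The SIDIAP controls cannot be selected by exactly the criteria used for IG-1 and IG-2, and the heart-failure code is wider than its criterion

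*Protocol article*

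**What the plan says.** All references are to the Protocol article.

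- **Study design** describes the SIDIAP group as an additional comparator, alongside IG-2, drawn from anonymised records of non-participating centres. It states that these patients are chosen by the trial's own criteria.
- **Evaluation of the effectiveness in the three study groups** says that the "population of all three types of learning centres that meet the defined criteria for inclusion and exclusion will be compared" and then that "Criteria will be adequately defined using the ICD-10 codes, thoroughly specifying the temporary windows of the accepted values". It limits this evaluation to outcomes available in SIDIAP.
- **Characteristics of participants** lists the exclusions. Among them are "T2DM controlled by endocrinologist at the moment of inclusion", "estimated life expectancy < 2 years, active treatment for malignancy", "class III or IV (New York Heart Association functional classification) heart failure (ICD-10: I50" and "any conditions that the investigator considered could prevent the patient from completing the study".
- **Table 1**, first row, gives the e-CRF as the source of the eligibility criteria for IG-1 and IG-2, and SIDIAP for controls. The Data collection section confirms that everything known about controls comes from SIDIAP.
- **Study variables** includes, as a recorded item, "presence of macrovascular complications (ischaemic heart disease, stroke, peripheral vascular disease, and heart failure". Table 1 gives SIDIAP as the source of this item in controls.

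**The concern.** A control group taken from a database is useful to the extent that its members could have been enrolled at an intervention centre. The plan asserts this, but it screens the two sides through different sources. Some criteria depend on a clinician's judgement about a patient, and no clinician screens the controls. One criterion is tied to a code that covers more patients than the criterion does.

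At stake is the comparison of IG-1 and IG-2 with usual care. If the control draw keeps patients whom an intervention centre would have refused, or drops patients whom it would have accepted, part of any difference in HbA1c, blood pressure, complications or costs would reflect selection. Regression or propensity-score adjustment, as foreseen in the Statistical analysis plan section, works only on what is recorded and only where the groups overlap.

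**Working it through.** The plan gives no figure on this point, so the check sets the sections side by side.

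**1. Which exclusions carry a code.** In Characteristics of participants:
- Three have an ICD-10 code: heart failure (I50), drug or alcohol abuse (F10-F14) and haemoglobinopathies (D58.2).
- Two have an ATC code: systemic glucocorticoids (H02AB) and orlistat (A08AB01).
- About eleven have neither: endocrinologist control, life expectancy, malignancy treatment, serious mental disorder, dementia, renal transplant or dialysis, pregnancy or lactation, immunosuppressants, chronic anaemia, BMI above 45, and investigator opinion.

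**2. Which of the eleven cannot be reproduced from records.** Most can be found through diagnoses, prescriptions or measurements, and an article need not print every code. Three are of another kind:
- Life expectancy under 2 years is a clinical estimate.
- Investigator opinion needs an investigator, and controls have none.
- Endocrinologist control is a care status. It is not a diagnosis, but it may have a recorded proxy. The cost row "Urgent care, outpatient and hospital admissions" has only the e-CRF as its source and nothing for controls. The row above it includes referrals, with SIDIAP as the control source. A referral-based proxy is therefore possible, although Table 1 does not say whether the specialty is recorded.

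That leaves at least two exclusions that operate in IG-1 and IG-2 and cannot operate in controls.

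**3. Heart failure.** The criterion excludes NYHA III-IV, so class I-II patients may be enrolled. This agrees with heart failure being a recorded complication. The attached code I50 carries no class. There are two ways to use it in the control draw:
- Every I50 record is dropped. Controls then lose class I-II patients, while the intervention arms keep them. With no I50 among controls, there is no overlap on which to adjust.
- I50 only labels the disease, and class is judged separately. The plan names no SIDIAP field for class, so the rule for controls is undefined.

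**4. Does the evaluation section settle it?** It refers to the populations of all three types of centre, so it can be read as one coded rule for everyone. The enrolled participants, however, are those who passed e-CRF screening and consented (Participants section, Table 1). Nothing says that they will be screened again by the coded rule before the three-group comparison.

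**5. Size.** The shift in the control mean equals f × d. Here f is the share of controls who would have been refused at an intervention centre, and d is their difference in 12-month HbA1c change from the other controls. The documents give neither. For illustration only, assuming f = 10-25% and d = 0.3-1.0 points gives 0.10 × 0.3 = 0.03 to 0.25 × 1.0 = 0.25 points, against a design difference of 1 point in Sample size calculation. These inputs are assumptions, and the range is not an estimate. This formula does not cover the loss of eligible class I-II controls, for which the documents give no prevalence either. Keeping patients of short life expectancy would make controls sicker, and dropping mild heart failure would make them healthier, so the direction is open too.

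**The case against.** The strongest reply is that the evaluation section already applies one set of coded criteria to all three types of centre and promises definitions with time windows. A reader might infer from the ICD-10 sentence that controls and intervention patients are selected by different rules. That sentence does not say so. The difference arises from Table 1, the Participants section and the exclusion list, and the document leaves open which reading applies. This part of the reply stands, and it limits the point to what the plan fails to state about enrolled participants.

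Three other strong readings also go too far:
- That controls will contain no heart failure. Table 1 expects heart failure to be recorded in controls at months 0 and 12, and nothing says that every I50 record is removed. Removal is one possible use of the code.
- That specialist-managed patients necessarily remain among controls. SIDIAP referrals may allow them to be identified.
- That all exclusions without a printed code are uncodable. Most are not, and the code list may sit in the full protocol.

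It is also fair to say that the SIDIAP group is an additional comparator and that IG-2 is the stated control for IG-1. That limits the reach of the point. It does not make identical selection attainable, nor does it match I50 to NYHA III-IV.

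**Conclusion.** The point holds in limited form. The claim that the SIDIAP group meets the trial's own criteria cannot be exact: life expectancy and investigator opinion have no counterpart in anonymised records, and eligibility comes from different sources. The I50 code is wider than the criterion it accompanies, so a code-based draw could remove class I-II controls while intervention centres keep such patients. The plan does not say that one rule is applied to enrolled participants and controls alike.

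The size and direction of any bias cannot be estimated from the documents. The comparison of IG-1 with IG-2 is not affected, because both are screened through the e-CRF by the same criteria. The conclusion rests on the article as printed. A full extraction specification could settle the codes, but it could not supply a clinician's judgement for controls.

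**What to change.** For the three-group comparison:

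1. State that one SIDIAP-derived eligibility list is applied to enrolled IG-1 and IG-2 patients as well as to controls. This assumes that enrolled patients can be identified in SIDIAP. The Data collection section already plans to take their cost variables from there.
2. Reconcile I50 with the NYHA III-IV limit, and treat I50 the same way in every arm: either remove it from all arms for this comparison, or keep it in all and adjust for it.
3. Define endocrinologist-controlled diabetes by one recorded proxy used in all arms, such as a referral within a fixed window before month 0 if the specialty is recorded. Say that it is a proxy.
4. Qualify the statement in Study design by naming life expectancy and investigator opinion as criteria without a counterpart in controls.

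The cost is wording in the extraction specification and one limitation sentence. The control extraction is still described in the future tense. A few enrolled patients may leave the three-group comparison, but they stay in IG-1 versus IG-2. The change does not remove the separate difference that intervention patients consented and controls did not. A count of patients refused on judgement is not requested, because recruitment was due to end on 31 October 2017 and the article describes no screening log.

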### Sample size calculation

The sample size was calculated using the GRANMO v.7.12 (IMIM, Barcelona) programme. Considering an alpha risk of 0.05 and a beta risk of less than 0.2 in a bilateral contrast, it was necessary to include 72 patients in each group (intervention and control) to detect a difference equal to or greater than 1% of HbA1c [5] between the two groups. A common standard deviation of 1.46 [6] and a loss rate to follow up of 20% were assumed.

Considering that each physician/nurse that makes up the Basic Care Unit will coordinate their diabetic patients, a correction may be made due to a possible contamination in the analysis between individuals by assigning each Primary Care Team to intervention or control groups and taking into account the design effect. According to a study performed by our research group [16], we estimated that each GP would have 15 potential candidate patients with HbA1c > 9%. Assuming that the intra-class correlation coefficient for Primary Care is 0.05 [29], resulting in a 1.7 design effect, the required sample size will be 42 * 1.7 = 72 individuals in each group.

Each control or intervention group consists of 3 basic health areas, one in each geographical area, each with a mean of 10 BCUs and 15 individuals per basic care unit. Thus, the sample finally calculated to obtain statistical significance was 72 subjects per centre, leading to a total of 648 study subjects.

First patient enrolled in the study INTEGRA on 09/12/2015.

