**Methods:**

This is a two-phase mixed method study, whose aims are the development of complex interventions and the assessment of their effectiveness. The main study outcome is a change in glycated haemoglobin (HbA1c) levels.

The INTEGRA study is divided into two phases. Phase 1: A qualitative study with a phenomenological approach using semi-structured interviews with the objective of determining the factors related to the participants and health care professionals that influence the development and implementation of a specific intervention strategy aimed at patients with poor glycaemic control of T2DM in primary care. Phase 2: Exploratory intervention study to be conducted in Primary Health Care Centres in Catalonia (Spain), including 3 specific health care areas.

The intervention study has two arms: Intervention Group 1 and 2. Each intervention group will recruit 216 participants (the same as in the control group) between the ages of 30 and 80 years with deficient glycaemic control (HbA1c > 9%). The control group will be established based on a randomized selection from the large SIDIAP (Sistema d’Informació per al desenvolupament de la Investigació en Atenció Primària) database of patients with comparable socio-demographic and clinical characteristics from the three provinces.

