#### Phase 2: Interventional study

##### Design

A controlled, non-randomized interventional study that involves primary care centres of 3 health care districts in Catalonia (Lleida, Girona, and Barcelona).

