#### Control group

The control group will consist of a randomized selection of patients who meet the inclusion criteria and have the same sociodemographic and clinical characteristics as the patients from the intervention groups, including the three participating health care districts. Patients allocated in this group will receive routine clinical care with the usual control by the family doctor and nurse according to the current Catalan Health Institute protocol. The data of patients in the control group will be obtained from the electronic medical record (SIDIAP) database [23]. The inclusion period for the control group will be from 9 December 2015 (the date when the first patient entered the study) until 31 October 2017 (end of the recruiting period). Data on diabetic status, glycaemia and all other study variables that were recorded in the electronic health records for patients in the intervention groups will be extracted from the SIDIAP database for 12 months for each patient. Participants will be followed up until they experience the outcomes of interest, die, leave the SIDIAP database (e.g., change of address) or complete the follow-up (31 October 2018). If the intervention groups reach the study sample earlier than 31 July 2017, the data for the control group will be followed until 12 months from the date when the last patient would be enrolled in the intervention group.

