### Statistical analysis plan

For data analysis, the IG-1, the IG-2, and the control group will be compared. All analyses will be carried out using bilateral tests with a nominal significance level of 0.05. However, if the comparisons obtain a *p*-value of less than 0.10, they will also be discussed as indicative of trends. Initially, basal characteristics of all groups will be evaluated to establish homogeneity in age, socio-demographic, comorbidities, laboratory parameters, concomitant medication and diabetes complications. An initial, descriptive comparison between groups of all variables will be performed to evaluate their baseline balance. Statistical significance will be assessed by the chi-square or t-test between the groups. Exploratory analyses will be applied when necessary.

The main variable is set as the difference in mean HbA1c values between the final visit and baseline. The difference will be evaluated in terms of the evolution of HbA1c as contrasted between groups by paired t-Student, or if the assumption of normality is not met for the right non-parametric.

If differences in the characteristics of the patients in each group are observed in the descriptive section of the study, a linear regression of the main variable (parameter evolution during the study) will be adjusted. This linear regression adjusted for the variables identified in the descriptive section, or the ability to adjust the model by setting a propensity score, will be evaluated. For all models, the distribution of waste will be studied, as well as the coefficient of determination (R2), to check for the correct setting.

As was done in Vinagre et al. [4], a subgroup analysis will be performed by a) gender (male / female), b) age: < age 65 / ≥ 65, and c) according to HbA1c control levels (< 10% / ≥ 10%).

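### District is built into every group but appears in no stated HbA1c analysis, so a between-group difference in district mix could confound the contrasts with no adjustment for district specified

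*Protocol article*

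**What the plan says.** Design. The study setting and design sections place the trial in Lleida, Girona and Barcelona. The sample size section adds that "Each control or intervention group consists of 3 basic health areas, one in each geographical area". That makes nine areas: one IG-1, one IG-2 and one control area in each district. The target is "72 subjects per centre, leading to a total of 648 study subjects", which is equal by district if it is met.

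Controls. Under Control group, "The control group will consist of a randomized selection of patients who meet the inclusion criteria". The same sentence goes on to say that they share the sociodemographic and clinical characteristics of the intervention patients, and it mentions the three participating districts. It gives no number or ratio per district.

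Analysis. The Statistical analysis plan section starts with a baseline comparison: "Initially, basal characteristics of all groups will be evaluated to establish homogeneity in age, socio-demographic, comorbidities, laboratory parameters, concomitant medication and diabetes complications". District is not in that list. Study variables gives only age and sex under sociodemographic variables, and neither that section nor Table 1 names district or centre. The primary contrast is a t-test, or a non-parametric test, on the change in HbA1c between groups. A linear regression or a propensity score follows if patient characteristics are found to differ. The logistic model for HbA1c below 7% has group indicators plus selected factors or a propensity score. The planned subgroups are sex, age and HbA1c level.

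**The concern.** A factor used to build the groups would normally be carried into the comparison of those groups. Here it is not, and the only route by which it could enter is a baseline screen that does not list it.

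The study is non-randomized, so no allocation mechanism protects the balance of districts between groups. The 72 per centre is a recruitment target. Loss to follow-up (assumed at 20%) may vary by area, and the SIDIAP draw has no stated quota. Districts may plausibly differ in case mix and practice; the protocol gives each its own hospital endocrinology contact. If the groups ended up with different district mixes, part of any difference between districts in HbA1c change would be read as an intervention effect.

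**Working it through.** **1. The plan's own figures.** Inputs from Sample size calculation: difference 1 point, SD 1.46, two-sided alpha 0.05, power 0.80, loss 20%, 15 patients per care unit, intra-class correlation 0.05.

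- Per group: 2 × (1.46 × (1.960 + 0.842))² / 1² = 33.5.
- With loss: 33.5 / 0.8 = 41.8, that is 42.
- Design effect: 1 + (15 − 1) × 0.05 = 1.7.
- 42 × 1.7 = 71.4, that is 72. Then 72 × 9 = 648 in total and 72 × 3 = 216 per group.

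The stated numbers reproduce. The design effect concerns the care unit, not the district.

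**2. Bias of a pooled contrast.** Bias = sum over districts of (share in group A − share in group B) × district mean HbA1c change. It is zero if the shares are equal (the plan), if the same imbalance occurs in both groups, or if districts do not differ in HbA1c change.

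**3. Size under assumptions.** The document gives no district effect, so every effect below is assumed.

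| Scenario | Assumed district effect | Bias (points) |
|---|---|---|
| IG-1 100/72/44, IG-2 44/72/100 | one end district differs by 0.3 to 0.5 | (100 − 44)/216 × 0.3 to 0.5 = 0.08 to 0.13 |
| Controls 60/20/20% against one third each | the over-drawn district differs by 0.3 to 0.5 | (0.60 − 0.333) × 0.3 to 0.5 = 0.08 to 0.13 |
| 60/72/84 against 72/72/72 | range 0.2 to 0.6 across districts | (84 − 60)/216 × half the range = 0.01 to 0.03 |
| 48/72/96 against 72/72/72 | range 0.2 to 0.6 across districts | (96 − 48)/216 × half the range = 0.02 to 0.07 |
| Loss 10/20/30% in one group, 20% throughout in the other | range 0.2 to 1.0 across districts | 0.008 to 0.042 |

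The last row uses retained shares of 0.375, 0.333 and 0.292, so the bias is (0.375 − 0.292)/2 × range. In the first row, if the deviating district is the middle one (72 in both groups), the bias is zero.

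**4. Effect on the test.** Patients analysed per group: 216 × 0.8 = 173. SE of the difference = 1.46 × √(2/173) = 0.157; times √1.7 = 0.205. With no true effect, the two-sided rejection rate at a nominal 5% is:

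| Bias | SE 0.157 (design effect 1) | SE 0.205 (design effect 1.7) |
|---|---|---|
| 0.08 | 8.0% | 6.8% |
| 0.13 | 13.1% | 9.7% |

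The right-hand column uses the protocol's own design effect and is the relevant one.

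**5. After the change.** If district effects are additive, a district term makes the contrast within district and this bias becomes zero. The stated sample size does not change.

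**The case against.** A reader might infer that unequal recruitment, loss or control sampling by district would in itself bias the contrasts, with nothing to correct it. The document does not support that, for four reasons.

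- Both conditions are needed: a mix that differs between groups, and districts that differ in HbA1c change. The document shows neither. It plans equal numbers per centre and areas chosen to be similar. This stands, and it makes the point conditional.
- The control-group wording can be read as making district one of the characteristics that controls share with intervention patients. It can also be read as mere coverage of the three districts. A strongly lopsided draw is not what the text describes, but no rule excludes one.
- The article plans a descriptive comparison of all variables, then regression on those found to differ, or a propensity score. District is not excluded, and case-mix differences would partly be caught through comorbidities, laboratory values and medication. What remains is that nothing requires a district term, and a known design factor should not depend on a baseline screen.
- It is tempting to blame laboratories, since the article refers to "laboratory variables according to the standard procedures of the laboratory of reference". It does not say that laboratories differ by district, and a constant laboratory offset largely cancels in a within-patient change. This argument is not relied on.

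It may also be said that covariates belong in a fuller analysis plan that is not shown. But the article has its own analysis section, which names the primary test and the trigger for adjustment. The point is an improvement to that stated method; the article contains no false statement or contradiction here.

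**Conclusion.** The point holds in a limited form. The groups are built in district blocks, the stated HbA1c analyses do not carry the block, and control numbers by district are not fixed. Confounding by district is possible and no adjustment for it is specified; it is neither shown nor certain.

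Under the planned equal numbers the bias is zero. Under assumed district differences of 0.3 to 0.5 points with extreme opposite splits it is 0.08 to 0.13 points, with the error rate at about 7 to 10% for a design effect of 1.7. The 13% figure requires ignoring the protocol's design effect. Milder splits give about 0.01 to 0.07 points. Even the largest of these is small against the 1-point target. The reason to act is that the remedy costs almost nothing and makes the analysis match the design.

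**What to change.** Include district as a prespecified three-level fixed factor in the linear and logistic HbA1c models, whatever the baseline tests show. Draw the SIDIAP controls in the same district proportions as the intervention patients, and state those proportions in the control-group section.

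The cost is one sentence of analysis wording, one sampling rule and 2 degrees of freedom. With care units as clusters (about 30 per group, so 58 degrees of freedom falling to 56 in a two-group contrast), the critical t is 2.00 either way. If the nine areas are the analysis units, degrees of freedom fall from 6 to 4 and the critical t rises from 2.45 to 2.78; there the district term is better kept as a sensitivity analysis.

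A district term does not deal with clustering at area level. With one area per group in each district, it cannot separate an area's own effect from that of the intervention. That is a separate point.
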